### Study design

The study consists of two components: (1) refining the prototype TI-MBCT and (2) conducting a feasibility trial for an RCT for TI-MBCT for DVA survivors with PTSD.

#### Intervention refinement

The intervention refinement work is informed by the Medical Research Council (MRC) framework for the development and evaluation of complex interventions [31, 32] and prior research in the field of developing psychological interventions [33–35]. This study component will involve
An update of the 2014 literature review on adapting mindfulness programs for PTSD and DVA populations.A qualitative study with women who have experienced DVA and professionals about using psychological interventions (including mindfulness-based approaches) for the treatment of PTSD in this population.A consensus exercise with mindfulness experts on areas of uncertainty regarding the proposed adaptations to a standard MBCT program.

Findings from these three sources will be synthesized to produce the TI-MBCT prototype 2 intervention which will be tested and refined further in the subsequent feasibility trial.

#### Feasibility trial

This study component comprises of a cycle of further refinement of the prototype TI-MBCT intervention through piloting and concurrent formative process evaluation. The direct experience of delivering and receiving the adapted TI-MBCT curriculum will feed into further intervention refinement in an iterative and systematic way. We will carry out a parallel-group, individually randomized, 2-arm feasibility trial with an embedded mixed-method process evaluation and economic evaluation (see Fig. 1).

**Fig. 1. Fig1:**
[figure not shown]
Flow diagram of randomized feasibility trial of two consecutive TI-MBCT groups vs NHS IAPT service https://www.spirit-statement.org/. TI-MBCT trauma-informed mindfulness-based cognitive therapy. NHS National Health Service. IAPT Improving Access to Psychological Therapies. PTSD Post-traumatic stress disorder

From the pool of service users in third sector DVA agencies, women with PTSD will be recruited and randomized (2:1—intervention:control). The participants in the intervention arm will take part in a group-based TI-MBCT course and participants in the control arm will be asked to self-refer through the IAPT service. Participants will be followed up at 6 months post-randomization. In the intervention arm, we will run two consecutive TI-MBCT groups. The first group will receive the TI-MBCT prototype 2 produced through the intervention development phase. At the end of the first group, we will interview the participants to inform further intervention refinement and produce the TI-MBCT prototype 3 for the second intervention group. After the second group, we will invite participants to take part in further qualitative interviews, as part of a process evaluation. Results of the feasibility trial and process evaluation will inform a decision on progression to a full-size trial. If we find that it is feasible and acceptable to progress (see Table 1), we will produce a final version of the TI-MBCT manual for the full-size trial.

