#### Feasibility trial

The required sample size is based on the precision for estimating the proportion (30%) of eligible participants consenting to participate in the study. If 120 eligible women are screened, then a true recruitment rate of 30% (= 36 recruits) will be estimated as between 21.8 and 38.2%, with 95% probability. This estimate is based on a previous trial that successfully recruited women from one of the collaborating DVA services [27, 52]. Based on previous trials of psychological interventions for women who have experienced DVA [27, 28] up to 33% of the consented and randomized participants are expected to drop out before the start of the mindfulness group/control intervention. Therefore, 54 will be randomized in order to be left with 36 who will be allocated to the intervention or control arm. We will compare the rate of drop out before starting mindfulness/control interventions between the two arms of the trial.

Retention will be optimized using established methods for trials involving women who have experienced DVA, [53–55] further modified through previous research in the UK context [56, 51], which resulted in 70–81% retention rates. The methods include maintaining a safe contact list, reimbursement for travel, childcare and £20 shopping voucher for each treatment session attended.

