#### Feasibility trial

Participants will be recruited through convenience sampling from a pool of service users in collaborating third sector organizations providing health and social care to DVA victims and survivors. The participants will be recruited in cohorts during a 2-month time-frames prior pre-scheduled TI-MBCT group dates:
Near the time of exit from the service, support workers will approach women at individual sessions with study information and invitationsGroup work facilitators will approach women at the end of the group with study information and invitationsAfter women exit the service, support workers will approach them during a 6-month follow-up phone call with study information and invitationsInvitations will be sent to women from the waiting list of the agency services.

All service users undergo risk assessment within the service by their support workers. Support workers will carry out initial screening (Table 2). Those meeting the criteria and willing to be contacted by the study researcher will be referred to the study for final screening (Table 2). Participants will receive the participant information sheet and consent form in advance, and the study researcher will obtain informed written consent.

Randomization will be independent of the study researcher. Once informed consent has been secured and baseline data has been collected, the researcher will telephone a remote randomization service at the Bristol Randomised Trial Collaboration (BRTC) to ascertain the participant allocation: either to the intervention arm (mindfulness) or control arm (IAPT) in a 2:1 ratio, so that each participant has a 2/3rd’s probability of receiving the mindfulness intervention. The participant will be informed which arm she is assigned to by the researcher. Randomization will happen in blocks of 6. For every 18 participants that are randomized, we anticipate that six will drop out before the start of the intervention, four will continue in the study as controls and eight will continue in the study in the intervention arm—this will be sufficient to run a mindfulness group.

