### Interventions

#### Intervention arm: TI-MBCT

The intervention will be group-based TI-MBCT developed through the intervention refinement phase of the study (see Table 3). The focus of this intervention is creating a new relationship with trauma-related phenomena and learning how to respond when the trauma of the past shows up in the present. TI-MBCT addresses the re-experiencing and reactivity characteristic of people who have experienced DVA with PTSD through the gradual development of skills for “de-centering” from distress. Instead of avoiding or becoming overwhelmed by distressing thoughts, powerful impulses, intense feelings, and disturbing body sensations, participants gradually learn to approach such experiences without judgment and with more acceptance and to gently ask “given that this experience is happening right now, how can I best take care of myself?” The cultivation of a non-judgemental attitude to what is arising in the present moment enables a way of responding, rather than reacting, to the self when trauma-related distress is experienced. In addition, being part of a group allows for a recognition that distress arising from past abuse is a shared experience, which reduces the sense of identification with being “damaged” that many people who have experienced DVA feel ([name]: How can an adapted MBCT course meet the specific vulnerabilities of women survivors of domestic violence and abuse? Unpublished thesis: Bangor University; 2015).

**Table 3 Tab3:** TI-MBCT intervention overview

TIDieR* item	Description
Brief name	Trauma informed mindfulness-based cognitive therapy (TI-MBCT) [58, 59]
Why	TI-MBCT addresses the patterns of avoidance, re-experiencing, and reactivity characteristic of people who have experienced DVA with PTSD through the gradual development of skills for managing overwhelm and developing skills for “decentering” from distress
What	The manual, mindfulness practices and exercises for TI-MBCT will be developed through the intervention refinement process.
Who provided	An experienced mindfulness teacher with expertise in trauma, who is in supervision with a mindfulness-based supervisor with expertise in trauma.
How	TI-MBCT delivered in face-to-face groups of up to nine participants
Where	A site will be selected which is safe and convenient for both participants and the therapist (e.g., community centre).

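### Randomising 54 women 2:1 sends 36 to TI-MBCT, but two groups of at most nine hold 18, so at least six expected starters have no place

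*Protocol article*

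**What the plan says.** Four parts of the protocol article bear on this.

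- **Number of groups.** The text under Fig. 1 (Study design, Feasibility trial) says "In the intervention arm, we will run two consecutive TI-MBCT groups". The first group receives prototype 2 and the second prototype 3. The Fig. 1 caption and the Qualitative analysis section also describe two groups.
- **Group size.** Table 3, row How: "TI-MBCT delivered in face-to-face groups of up to nine participants".
- **Number randomised.** The Sample size section, Feasibility trial, assumes that "up to 33% of the consented and randomized participants are expected to drop out before the start of the mindfulness group/control intervention" and concludes: "Therefore, 54 will be randomized in order to be left with 36 who will be allocated to the intervention or control arm".
- **Yield per group.** The Recruitment and consent section, Feasibility trial, sets 2:1 allocation in blocks of six. It expects six of every 18 women randomised to drop out before starting, so that "four will continue in the study as controls and eight will continue in the study in the intervention arm". It regards those eight as enough for one group.

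Table 1 takes the women randomised to the intervention arm as the uptake denominator (green > 70%, amber 50–69%, red < 50%). It judges retention as the proportion of the intervention arm receiving at least four sessions (green ≥ 60%).

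**The concern.** The number randomised, the allocation ratio, the number of groups and the group cap cannot all hold. The figures 54 and 36 are three times the per-group yield (3 × 18 randomised, 3 × 12 continuing), while the rest of the article describes two groups. It mentions no third group, parallel group or waiting list for the surplus.

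Two progression criteria depend on this. If 54 women are randomised, uptake and four-session retention are limited by the number of places. A low value would then partly measure supply rather than willingness to join or stay, which is what Table 1 is meant to capture. If recruitment stops when the two groups are full, the stated sample size is not the one the design delivers.

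**Working it through.** **Inputs.** 54 randomised, up to 33% pre-start loss, 30% recruitment from 120 eligible women (Sample size section); 2:1 allocation and 18 randomised per group (Recruitment and consent section); two groups (text under Fig. 1); at most nine per group (Table 3); thresholds (Table 1). Loss is taken as equal in both arms, which matches the protocol's own 8:4 split.

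**1. Reproduce the stated figures.**
- Inflation for dropout: 36 / (1 − 1/3) = 54. Reproduced.
- Interval for 30% of 120: 0.30 ± 1.96 × √(0.30 × 0.70 / 120) = 21.8% to 38.2%. Reproduced.
- Per group: 18 × 2/3 × 2/3 = 8 intervention starters and 18 × 1/3 × 2/3 = 4 controls. Reproduced.

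Each figure is right by itself. The conflict appears when they are combined.

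**2. Places against starters with 54 randomised.**
- Allocated to TI-MBCT: 54 × 2/3 = 36. Control: 18.
- Expected TI-MBCT starters: 36 × 2/3 = 24, or 12 per group against a cap of nine.
- Places: 2 × 9 = 18. Shortfall: 24 − 18 = 6, and 6/24 = 25%.

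Both 33% and nine are stated as upper limits, so six is the smallest expected shortfall:

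| Pre-start loss | TI-MBCT starters | Without a place |
|---|---|---|
| 33% (as 1/3) | 24 | 6 |
| 25% | 27 | 9 |
| 20% | 28.8 | 10.8 |
| 0% | 36 | 18 |

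To fit 18 places, loss in the arm would have to reach 1 − 18/36 = 50%. If each of the 36 women starts independently with probability 2/3, the chance of more than 18 starters is 0.97.

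**3. Effect on Table 1 with 54 randomised.**
- Highest possible uptake: 18/36 = 50%, the bottom of amber. Green needs more than 0.70 × 36 = 25.2, so at least 26 women.
- Highest possible retention, with all 36 as denominator: 18/36 = 50%. Green needs at least 0.60 × 36 = 21.6, so at least 22 women.
- At the working group size of eight: 16/36 = 44% uptake, which is red.

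**4. What would fit.**
- Groups needed for 54 under the protocol's rule: 54/18 = 3, with 3 × 9 = 27 places for 24 starters.
- Number randomised that fits two groups under the same rule: 2 × 18 = 36. This gives 24 to TI-MBCT, 16 starters and eight per group. The capacity ceiling on uptake becomes 18/24 = 75%, so green is attainable.
- The outer limit at nine per group is 40 randomised (40 × 2/3 × 2/3 = 17.8); 41 gives 18.2.

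**5. A likely source of the mismatch.** The Sample size section uses 36 twice. It is first the number recruited from 120 ("a true recruitment rate of 30% (= 36 recruits) will be estimated as between 21.8 and 38.2%, with 95% probability") and then the number left after dropout. If 54 are randomised at 30% recruitment, 54/0.30 = 180 eligible women are needed, not 120.

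**The case against.** The strongest points on the other side are these.

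- **The 50% ceiling assumes randomisation continues past capacity.** Recruitment runs in cohorts before pre-scheduled group dates, so the team may simply recruit fewer than 54. That is plausible, but then the stated sample size is wrong. The conflict changes form and remains.
- **The Sample size section, read literally, allocates only the 36 women left after dropout.** The intervention arm would then be 24, and 18/24 = 75% would be green. The Recruitment and consent section contradicts this, because there dropout follows randomisation. Even on the literal reading, 24 women face 18 places.
- **Table 1 sets green recruitment at 24 women, not 54.** With 24 randomised, 16 go to TI-MBCT and about 11 start, which fits two groups. This shows that the trial could run within its capacity. It does not make the target of 54 deliverable.
- **A shortage of places would be noticed.** Acceptability has its own qualitative criterion, participants are interviewed, and an independent steering group is consulted. This stands in part: outright misreading is not certain. The numerical criteria would still be capped and would need reinterpretation after the fact.
- **Only the uptake criterion explicitly names those randomised as denominator.** This stands. The retention cap depends on reading the intervention arm as all women randomised to it.
- **The document does not show which figure is wrong.** This also stands, and it is why the fix offers two routes.

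**Conclusion.** The concern holds. With 54 randomised at 2:1 and two groups of at most nine, at least six of 24 expected TI-MBCT starters (25%) have no place. Uptake cannot exceed 50% against a green threshold above 70%. Retention is capped at 50% as well if all women randomised to the arm form its denominator.

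This assumes equal loss in both arms, no groups beyond the two described, and that taking up the group means having a place in it. The uptake ceiling applies only if all 54 are in fact randomised; otherwise the error lies in the stated sample size.

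Removing the capacity limit would not by itself make green likely. The protocol's own 33% loss implies expected uptake of about 67%, which is amber. That result would reflect participants' choices and not the number of places.

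**What to change.** State one number randomised, with a number and size of groups that can hold it. Carry it through the Sample size section, the Recruitment and consent section, the text and caption of Fig. 1, Table 3 and the Qualitative analysis section. Two routes are consistent with the protocol's own figures.

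- **Two groups, 36 randomised.** 24 women go to TI-MBCT and 12 to control, with about 16 and 8 starting, so eight per group. This agrees with 30% of 120 eligible women and is a whole number of blocks of six. The cost is precision, and the aim of having 36 women left after dropout is given up, since 24 would remain. At an uptake of 2/3, the 95% half-width grows from 1.96 × √(0.222/36) = 15 percentage points to 1.96 × √(0.222/24) = 19.
- **54 randomised, three groups.** The third group must be stated everywhere, including which prototype it receives and when its data are analysed. The eligible pool should be restated as 180 at 30% recruitment. The cost is delivering one more group.

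The first route only restates figures and needs no extra delivery. On either route, the Sample size section should stop using 36 for both the number recruited and the number left after dropout, and should say that allocation comes before dropout.

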### Study setting

The study will be based at the University of Bristol.

#### Intervention refinement

Women who have experienced DVA and professionals will be recruited from non-NHS and NHS organizations, not limited by location. Interviews will take place at a location that is safe and convenient for both participant and researcher. The consensus exercise will be held on university premises.

#### Feasibility trial

Participants will be recruited from third sector DVA agencies in two local authorities in the southwest of England.

Study assessments and the TI-MBCT intervention will be delivered at locations that are safe and convenient for both participants and researchers, e.g., community centers. The control intervention will be delivered at NHS sites or non-NHS sites providing IAPT services for PTSD. Importantly, the intervention sites will be in geographical areas served by the participating third sector organizations from which the participants were recruited.

A safety protocol will be in place to protect the welfare of women who have experienced DVA participating in the trial. A safe method of contact will be agreed with the researchers, interviews will take place in a place safe for the researcher and participant, and under no circumstances will the researcher discuss any information with another person known to the participant.

### Eligibility criteria

The eligibility criteria for the *intervention refinement* process will be

Target population:
Female18 years or olderSelf-identified as victims or survivors of any forms of DVASelf-identified experience of mental health problem(s) including PTSD.

NHS-employed and non-NHS employed professionals:
Mental health care practitioners: mindfulness practitioners and therapists with experience of treating PTSD.DVA advocates from third sector organizations with experience of working with people who have experienced DVA and PTSD.Managers of NHS-based and non-NHS based services for women who have experienced DVA.

The eligibility criteria for the *feasibility trial* will be
Female18 years or olderAccessed collaborating third sector organizations providing health and social care to DVA victims and survivorsClinically important symptoms of PTSD [21] indicated by the baseline score above the clinical threshold on the Primary Care PTSD Screen (PC-PTSD-5). “Yes” to any exposure to traumatic events and “yes” to any three out of five items [36]

Women with and without children will be recruited to explore the feasibility of measuring mother-reported outcomes for children. If a woman has more than one child aged 8-18, the study investigator will use random number generation to select one child for the study to reduce the response burden on the woman.

The exclusion criteria for the feasibility trial are currently based on the standard MBCT guidance [37]; measures are summarized in Table 2:
Unable to provide written informed consentUnable to speak and understand English (because interventions will be delivered in English)Current drug or alcohol dependency (the full Alcohol Use Disorders Identification Test (AUDIT) score ≥ 20, the Drug Use Disorders Identification Test (DUDIT) score ≥ 25)Organic brain damageCurrent or past psychosisCurrent persistent self-harm or suicide riskAlready receiving psychological therapy

The inclusion/exclusion criteria for the feasibility trial will be revised and amended as necessary through the intervention refinement work.

**Table 2 Tab2:** Schedule of measures in a feasibility trial

Procedures	Initial screening	Final screening	Baseline	6-month follow-up
Socio-demographics (bespoke)	x			
Speaking and understanding English (support worker’s judgment)	x			
Diagnosed psychosis, bipolar disorder, personality disorder (from collaborating agency case record)	x			
Current psychological therapy (from collaborating agency case record)	x			
Readiness to start mindfulness group or alternative talking therapy on the NHS (woman’s own judgment)	x			
The Primary Care PTSD Screen for DSM-5 (PC-PTSD-5) [36]. Cut off: “Yes” to any exposure to traumatic events and “yes” to any three out of five items.		x		
The Alcohol Use Disorders Identification Test Consumption (AUDIT-C), if The score is ≥ 5, full AUDIT [38, 39]. Cut-off ≥ 20.		x		
The Drug use Disorders Identification Test (DUDIT) [40, 41]. Cut-off ≥ 25.		x		
Depression and suicidal ideation as measured by the Patient Health Questionnaire-9 (PHQ-9) [42, 43]		x		x
Suicide history as measured by question “I made plans to end my life in the last 2 weeks” (bespoke)		x		
Suicide history as measured by question “I made attempts to end my life in the last 12 months” (bespoke)		x		
Support you have received for mental health problems (bespoke)			x	
The Life Events Checklist for DSM-5 (LEC-5) Standard [44].			x	
The PTSD Checklist for DSM-5 (PCL-5) [44]			x	x
The International Trauma Questionnaire (ITQ) [45]			x	x
The Severity of Dissociative Symptoms—Adult (Brief Dissociative Experiences Scale [DES-B]—Modified) [46]			x	x
Brief screening version of the Childhood Trauma Questionnaire [30]			x	
Composite Abuse Scale Revised-Short Version (events in the last 12 and 6 months, respectively) [47]			x	x
Self-Compassion Scale–Short Form (SCS-SF) [48]			x	x
Generalized Anxiety Disorder-7 (GAD-7) [49]			x	x
EQ-5D-5L [50]			x	x
KIDSCREEN-10 Index. Health Questionnaire for Children and Young People. Parent Version [51]			x	x
Resource questionnaire (bespoke)				x

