Choice of the control intervention. In a definitive trial, the control intervention will be an evidence-based manualized psychological intervention for PTSD currently available within NHS Improving Access to Psychological Therapies (IAPT) services. Our primary intention was to use trauma-informed cognitive behavioral therapy (TI-CBT). However, consultations with service user and professional stakeholders revealed that in DVA agencies women with mental health problems are signposted to their GPs and IAPT services. The latter offers varied treatments (e.g., trauma counseling, TF-CBT, EMDR) depending on an individual’s symptoms and needs and practitioners’ availability.Recruitment of DVA survivors with PTSD through third sector DVA serviceThe randomization of DVA survivors with PTSDRetention of DVA survivors with PTSD in the trialUptake, retention, and acceptability of the modified MBCT intervention to DVA survivors with PTSDData collection methods.

The coMforT (Mindfulness for Trauma) study addresses these areas of uncertainty through further intervention development work with stakeholders followed by feasibility testing of the refined intervention.

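### Current psychological therapy is checked once, from the agency case record, although two of four recruitment routes reach women the agency is not currently working with

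*Protocol article*

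**What the plan says.** Under Eligibility criteria, the feasibility trial excludes women who are already in psychological therapy and women with current or past psychosis. That section refers the reader to Table 2 for the measures.

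Table 2 gives each of these exclusions one source and one time point. The therapy row reads "Current psychological therapy (from collaborating agency case record") and the psychosis row "Diagnosed psychosis, bipolar disorder, personality disorder (from collaborating agency case record"). Both are marked at initial screening only. Under Recruitment and consent, Feasibility trial, "Support workers will carry out initial screening (Table 2"). The study researcher's final screening consists of the PC-PTSD-5, AUDIT-C or full AUDIT, DUDIT, PHQ-9 and two suicide questions.

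The same section lists four recruitment routes. Two reach women in contact with the service: individual sessions ("Near the time of exit from the service, support workers will approach women at individual sessions") and the end of group work. The third reaches women who have left, when "support workers will approach them during a 6-month follow-up phone call". The fourth sends invitations to women on the agency waiting list.

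Table 2 also has a baseline item, "Support you have received for mental health problems (bespoke"). Allocation is requested "Once informed consent has been secured and baseline data has been collected", so this item is completed before randomisation.

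**The concern.** Whether a woman is in therapy now can change from month to month. A case record is a reasonable source while the agency is working with her. It is a weaker one after she has left or before the work has begun. The section on pre-protocol development also says that "in DVA agencies women with mental health problems are signposted to their GPs and IAPT services". Therapy begun after exit is therefore something the agencies' own practice encourages, and it may be therapy in the service that forms the control condition.

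Three planned results would be affected if such women were randomised:

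- **Control uptake.** Table 4 defines this as the proportion of the arm that self-referred to IAPT. A control already in IAPT either counts as uptake that the trial did not prompt, or counts as non-uptake while she is receiving the service.
- **Usual care.** The first feasibility objective is to learn which IAPT treatment could serve as the control and how practical referral is. A pathway that began before randomisation does not answer that.
- **Six-month outcomes.** Concurrent therapy in either arm enters the arm differences, and also the SDs intended for the full trial's sample size.

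**Working it through.** **1. Source of the check against route.** This comparison rests on the text alone.

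| Route | Relation to agency at approach | Named source for current therapy | Re-check at final screening |
|---|---|---|---|
| Near exit, individual session | in contact | case record | none |
| End of group work | in contact | case record | none |
| Six-month call after exit | has left | case record | none |
| Waiting list | service not yet received | case record | none |

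The source fits the first two routes. It fits the last two, 2 of 4, poorly. Table 2 distinguishes its sources elsewhere: English is by the support worker's judgement and readiness to start by the woman's own. The case record is therefore a stated choice for therapy, not a detail left out of a condensed article.

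**2. Number of controls.** Inputs are from Sample size, Feasibility trial: 120 eligible, 30% recruited, up to 33% dropping out before the start.

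- 120 × 0.30 = 36
- 36 / (1 − 0.33) = 53.7, rounded up to 54, which is the article's own figure
- With 2:1 allocation, 54 × 1/3 = 18 controls and 54 × 2/3 = 36 in the TI-MBCT arm

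**3. Weight of one woman.** Table 4 uses the number randomised in the arm as the uptake denominator.

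- One control: 1/18 = 5.6%
- One woman in the TI-MBCT arm: 1/36 = 2.8%

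**4. Number affected.** The expected number by the two routes is 54 × s × q. Here s is the share of recruits arriving by the post-exit and waiting-list routes, and q is the share of those women who are in therapy that the record does not show. The article gives neither. With assumed values only:

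- s = 0.25, q = 0.05: 54 × 0.25 × 0.05 = 0.7 women
- s = 0.75, q = 0.20: 54 × 0.75 × 0.20 = 8.1 women

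The spread shows that the answer is set by the assumptions. It is not an estimate.

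**The case against.** The other side has a good deal to say.

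- **Records.** The article does not say that records are out of date or empty for these women. On the post-exit route a support worker is speaking to the woman. Women on the waiting list may have an intake record, service users undergo risk assessment, and initial screening includes the woman's own view of her readiness. This stands: the gap in the record is an inference. But the readiness item does not ask about present therapy, and for therapy Table 2 points to the record and not to the conversation.
- **The baseline support item.** It is collected before the allocation call by the same researcher and could reveal current therapy. Nothing says that eligibility closes before baseline. This also stands, as a possible safeguard. However, the item carries no cut-off and no exclusion is tied to it.
- **Consequences.** The analysis is mainly descriptive and shows no p values. Each control's IAPT pathway and resource use are collected at 6 months, so a control already in therapy might be recognised afterwards. That limits the harm to interpretation but does not keep her from being randomised. Randomisation also means that such women do not systematically favour one arm; they blur the contrast.

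A reader might go further and infer that following Table 2 necessarily enrols excluded women, that women past exit are the group most likely to be in therapy, or that some 10–20% of those randomised would be ineligible. The documents support none of these. They show only that it could happen. The Background says that stigma reduces service use and that standard trauma treatment is hard for these women to access. Any percentage depends wholly on assumed route shares and therapy rates.

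A reader might also treat the psychosis exclusion as equally exposed. It is not: an older record still shows a past diagnosis. The point there is secondary and concerns mainly the waiting-list women.

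**Conclusion.** The point holds as a weakness in how an existing exclusion is ascertained. Table 2 fixes one source and one early time point for current therapy, two of the four routes fit that source poorly, and no later item is designated to catch what it misses. A woman already in therapy, possibly in the control service, could therefore be randomised. Each one allocated to control is about 5.6% of the control-uptake denominator, assuming the planned 54 randomised at 2:1. How many there would be cannot be computed from the article. No stated figure is wrong and the sample size does not change. The conclusion rests on one inference: that the record may not show current therapy for women the agency is not working with at the time. The change is worth making because it is cheap and because the same screening could pass into the definitive trial.

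**What to change.** At final screening, before randomisation, have the study researcher ask each woman whether she is currently receiving psychological therapy. Apply the existing exclusion to her answer as well as to the case record, and mark this in Table 2. Alternatively, designate the pre-randomisation item "Support you have received for mental health problems (bespoke") as an eligibility check, provided that it asks about present therapy, and state that it is reviewed before the allocation call.

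A matching self-report question on psychosis history is optional and matters mainly for women from the waiting list. The exclusion itself should stay as written: asking about therapy that is booked but not begun, and excluding on the answer, would widen it.

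The cost is one or two questions at a contact that already takes place and an edit to Table 2. The downside is that a few more women may be screened out.
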